## Methods

### Setting

The study will be conducted at four Comprehensive Cancer Centres in France (Institut Curie in Paris and Saint-Cloud, Centre Lacassagne in Nice, Institut Bergonié in Bordeaux, and Centre Paul Strauss in Strasbourg). The medical turnover of the different centres is variable, ranging from 1000 to 5000 new patients per year, with breast cancer accounting for around 50% of the primary tumours. Each centre has a PC team integrated into overall cancer care. Referral to the PC team is triggered by oncologists for advanced cancer patients, according to usual criteria, such as severe physical symptoms and/or psychosocial distress. PC delivery follows international guidelines and current best practices.

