**Primary caregiver**								
SCNS-P&C	X		X		X		X	

a if applicable

- The EORTC QLQ-C30 is a validated HRQoL questionnaire for cancer patients. This questionnaire generates fifteen HRQoL scores: one global health status score, five functional scores (physical, role, emotional, cognitive and social) and nine symptom scores (fatigue, nausea and vomiting, pain, dyspnea, insomnia, loss of appetite, constipation, diarrhoea and financial difficulties) [35]. Each score is standardized on a 0 to 100 scale, and a high of global health status, a high functional level, and a high symptomatic level.

- The PATSAT-C33 is a questionnaire on satisfaction with care, completed by a specific OUT-PATSAT7 module for ambulatory care [36, 37]. Both the questionnaire and module measure cancer patient satisfaction with the care provided by doctors and nurses, and their satisfaction with care organization and services.

-The HADS questionnaire is composed of 14 items, including 7 items related to anxiety and 7 to depression [38]. A score is generated for each dimension. These scores range from 0 to 21. A score from 0 to 7 corresponds to a normal level of anxiety-depression, 8 to 10 a moderate level of anxiety-depression and 15 to 21 a severe level of anxiety and depression.

- The PTPQ consists of 13 items evaluating patients’ information preferences, perceptions of prognosis, the aims of cancer treatments, and communication about end-of-life care [39]. The PTPQ evaluates patients’ beliefs regarding: 1) the probability of a cure, 2) the importance and usefulness of knowing the prognosis, 3) the main objective of cancer care, 4) preference for treatment information, and 5) satisfaction with the quality of information received on prognosis and treatment.

-The SCNS32-P&C-F questionnaire assesses the impact of care on the unmet needs of family members and caregivers who are the main source of emotional, physical and social support for patients on a daily basis [40, 41]. This questionnaire assesses the needs for information on care for their own health, their emotional and psychological needs, social needs, the consequences of illness at work, and communication and support needs. Each item is assessed using a score ranging from 1-no need for support to 4 unmet needs for support.

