### Statistical analysis

Assuming an improvement in the median time of non-deteriorating quality of life from 1 month to 2 months; with a bilateral Type I error of 0.0166 and a statistical power of 80%; for a ratio of 1: 1 (H0: HR = 1 / H1: HR = 0.5), the number of patients required is 96 to observe 88 events. With an attrition rate of 50% (patients lost to follow-up or prematurely deceased), the number of patients required is 144, meaning 72 patients in each arm.

The superiority of one type of care over the other will need to be demonstrated if at least one of the three HRQoL dimensions targeted show a significantly longer deterioration free survival compared to the other group without significantly shorter deterioration on at least one of the other two HRQoL dimensions [45, 46]. The scores for each dimension will be analysed separately. Quality of life survival deterioration free survival (QFS) will be defined as the time interval between inclusion in the study and the occurrence of the first clinically significant deterioration of at least 10 points from the baseline score, without further improvement of at least 10 points from the baseline score, or death [47].

The analysis of the primary endpoint will be performed at the statistical level α = 0.0166 and the analysis of the secondary endpoints will be performed at the level α = 0.05. The minimal clinically important difference will be defined as 10 points for each dimension of the QLQ-C30.

Analyses will be conducted in intent-to-treat and will include all randomized patients, and analysed according to the group they were assigned, regardless of what intervention they really received and the respect of not of eligibility criteria.

A secondary analysis will be carried out per protocol after exclusion of individuals presenting major deviations from the protocol and include patients who respect the intervention group allocated. The description of the patients for all socio-demographic and clinical characteristics, as well as the scores obtained on the different questionnaires will be based for the two intervention groups on the data collected at inclusion. The categorical variables will be expressed as absolute and relative frequencies and the continuous variables as means (standard deviations) or medians (min/max).

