QFS will be estimated according to the Kaplan-Meier method and described per group using the median and confidence interval at (100-α) %. The comparison between the two RCT groups will be performed using log-rank test. A univariate Cox model will be performed to estimate the Hazard Ratio coefficient and its confidence interval at (100-α) %. Multivariate Cox models will also be conducted to explore the factors influencing QFS. All clinical and socio-demographic variables collected at baseline will be tested in univariate analysis. Variables with a *p*-value < 0.20 will be eligible for the multivariate model. This model will consider the collinearity of the eligible variables and will be constructed according to the Peduzzi rule of one variable for 10 events. The group will be forced into the multivariate model. Overall survival is defined by the interval between the date of randomization and the occurrence of death whatever the cause. It will be estimated according to the Kaplan-Meier method and described per randomized groups using the median and 95% confidence interval, and compared between the two groups using the Log-rank test. A univariate Cox model will be performed to estimate the Hazard Ratio coefficient and its 95% confidence interval.

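### Patients with less than 10 points left to worsen at baseline can reach that dimension's QFS event only by dying, and the unstratified analysis lets them dilute its hazard ratio

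*Protocol article*

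**What the plan says.** All references are to the Protocol article.

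- **Event** (Statistical analysis): QFS runs from inclusion to "the occurrence of the first clinically significant deterioration of at least 10 points from the baseline score", provided there is no later 10-point recovery, or to death. Each of the three co-primary dimensions (global health status, fatigue, emotional functioning) is analysed separately.
- **Scale** (Patient-related outcomes): "Each score is standardized on a 0 to 100 scale".
- **Analysis set and test** (Statistical analysis): intention to treat, with every randomised patient. "The comparison between the two RCT groups will be performed using log-rank test", with a univariate Cox model for the hazard ratio. No strata are named.
- **Sample size** (Statistical analysis): an "improvement in the median time of non-deteriorating quality of life from 1 month to 2 months", "for a ratio of 1: 1 (H0: HR = 1 / H1: HR = 0.5", "with a bilateral Type I error of 0.0166 and a statistical power of 80" per cent. From this, "the number of patients required is 96 to observe 88 events".
- **Population** (Setting): oncologists refer "according to usual criteria, such as severe physical symptoms and/or psychosocial distress". Eligibility criteria set no limit on any baseline questionnaire score.

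**The concern.** A fixed 10-point worsening on a bounded scale is out of reach for a patient who starts less than 10 points from the bad end. Take a patient with fatigue 100 at baseline and at every visit to week 24, alive throughout. This patient has no fatigue event and counts as deterioration-free for the whole period at the worst possible score. A patient with emotional functioning 0 throughout who dies at month 5 has a QFS of 5 months on that dimension.

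Such patients carry no information on whether day-hospital care delays deterioration, yet they stay in both arms' risk sets and become a growing part of them as others have events. The hazard ratio for that dimension moves towards 1, and median QFS includes time spent at or near the worst score. Referral for severe symptoms or distress makes some such baselines plausible, particularly for fatigue and emotional functioning.

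**Working it through.** **1. The plan's own figures reproduce.** Schoenfeld's formula for 1:1 allocation is events = 4(z_α + z_β)² / (ln HR)². With two-sided α = 0.0166, z_α = 2.395; with 80% power, z_β = 0.842; and HR = 0.5. This gives 4 × 10.479 / 0.4805 = 87.2, so 88 events. Power at 88 events is Φ(√88 × 0.6931/2 − 2.395) = Φ(0.856) = 0.804.

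The 96 patients also fit. With exponential medians of 1 and 2 months over 24 weeks (5.52 months), the event probabilities are 1 − 2^(−5.52) = 0.978 and 1 − 2^(−5.52/2) = 0.852. Their mean is 0.915, and 96 × 0.915 = 87.9.

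**2. Who cannot deteriorate.** Fatigue worsens upwards, so the rule needs baseline + 10 ≤ 100, that is, fatigue at most 90. Global health status and emotional functioning worsen downwards, so it needs baseline − 10 ≥ 0, that is, at least 10. A patient exactly 10 points from the worst score can still have the event.

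**3. Assumptions for the size.** A share f of patients has no room to worsen. The article does not give f, so a range is shown. These patients can only die, with a median survival of 6 months in both arms (also assumed; the eligibility range is more than 2 and fewer than 12 months). The others have exponential QFS with medians of 1 and 2 months. Observation ends at 24 weeks with no other loss, and α is 0.0166 two-sided.

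**4. Why the ratio is diluted (f = 10%).** At 3 months, the control arm still at risk consists of 0.9 × 2^(−3) = 0.1125 able to worsen and 0.1 × 2^(−3/6) = 0.0707 not able. The second group is 0.0707/0.1832 = 39% of the risk set. In the day-hospital arm the first figure is 0.9 × 2^(−1.5) = 0.318, so the share is 0.0707/0.389 = 18%.

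The medians move less. Solving 0.9 × 2^(−t) + 0.1 × 2^(−t/6) = 0.5 gives t = 1.13 months instead of 1. The same equation with 2^(−t/2) in the first term gives 2.18 months instead of 2.

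**5. Simulated power per dimension.**

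| Share without room | 96 patients, unstratified | 96, stratified | 144 fully followed, unstratified |
|---|---|---|---|
| 0% | 80% | 80% | 94% |
| 3% | 71% | 78% | 90% |
| 5% | 67% | 76% | 86% |
| 10% | 54% | 71% | 75% |

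Stratified means a log-rank test stratified by whether a 10-point worsening is possible at baseline. Independent runs agree to within about 1 percentage point. The unstratified hazard ratio is about 0.53 to 0.55 at 5% and 0.57 to 0.58 at 10%, depending on the horizon and how it is computed. Most of the loss is dilution: over a 6-month horizon, expected events fall only from 89 to 85 at a 10% share.

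**6. Sensitivity at a 10% share, 96 patients.** With a 6-month horizon, unstratified power runs from 66% to 48% as the assumed median survival of the affected patients goes from 2 to 12 months. If death also has a hazard ratio of 0.5, power is 61%. Type I error is essentially unchanged, at about 2% for both tests.

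**The case against.** **An article may leave this to the SAP.** Handling of patients at the end of the scale often sits in the full protocol or SAP, neither of which is shown. If a rule exists there, the sponsor need only cite it. But the article itself fixes the event, the scale, the analysis set and the test, and together these produce the problem.

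**The sample size might seem to assume that everyone can deteriorate.** A reader might infer this from 88 events in 96 patients, or 92%. It does not follow. Death is an event, so every patient can have one, and the 92% shows only that exponential medians of 1 and 2 months were used.

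**The stated power might seem not to be delivered even if the planning assumption is right.** The article does not support that either. It states a hazard ratio of 0.5 for the trial comparison, without restricting it to patients able to worsen. If 0.5 is true among all randomised patients, 88 events give 80%. The calculation above applies 0.5 to a subset and adds patients with no effect, which is a weaker overall effect. Matching only the medians is not enough, however: with whole-population medians held at 1 and 2 months and these patients included, the hazard ratio is no longer constant, and unstratified power with 96 patients was about 69% at a 5% share and 57% at 10%.

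**The share may be small.** Entry requires performance status 2 and the ability to answer questionnaires, and excludes severe psychopathological disorders, which bears on emotional functioning. This stands: no baseline distribution is given.

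**The effect is per dimension.** A patient at the worst fatigue score can still deteriorate on the other two, and one significant dimension can suffice provided that neither of the others is significantly worse. This also stands. The figures are not the probability that the trial succeeds.

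**There may be a reserve.** With 144 fully followed patients, power stays above 80% at shares of 3% and 5%. But the article plans for 50% attrition, and 144 × 0.5 = 72, so this reserve cannot be relied on.

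**Conclusion.** The point holds as a gap in the endpoint and analysis rules; it does not show that the trial is underpowered. It is certain that a patient with less than 10 points left can have that dimension's event only by dying. In the modelled setting, where treatment delays deterioration among those able to worsen, including such patients moves the hazard ratio towards 1 and lengthens median QFS. The size is conditional. The figures of 71%, 67% and 54% rest on assumed shares of 3%, 5% and 10%, 96 evaluable patients, a hazard ratio of 0.5 confined to patients able to worsen, and 6-month median survival with no treatment effect on death in the others. The test remains valid. What is at risk is sensitivity on the affected dimension and the meaning of its median.

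**What to change.** Unless the full protocol or SAP already has a rule, in which case cite it:

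1. For each dimension, define a baseline indicator of whether a 10-point worsening is possible: fatigue at most 90; global health status and emotional functioning at least 10.
2. Stratify that dimension's QFS log-rank test and Cox model by the indicator. All randomised patients stay in the analysis, and those without room to worsen are compared only with each other, on death.
3. Report the number without room to worsen by arm and dimension.
4. Give the Kaplan-Meier median for patients able to deteriorate beside the overall median.

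Cost: a short addition to the analysis plan, using the baseline QLQ-C30 already scheduled, with no new data or patients. One stratum per dimension will be small (about 5 of 96 patients at a 5% share), about 1 percentage point of power is lost if stratification proves unnecessary, and one more median is reported per dimension. Settle the rule before outcome data are examined by arm.

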### Randomisation

Patients are randomized between the PCDH group (experimental group) and standard outpatient PC group (control group). Assignment is determined by the random generation of a 1:1 randomization sequence. Randomization is performed by minimization, with stratification according to the following criteria:

- The cancer centre, as unknown heterogeneity in PC management could induce a bias.

- The presence or absence of a designated person close, to obtain a well-balanced population in the two groups, enabling valid statistical analyses for the caregiver-related outcomes.

- The main indicators influencing prognosis and HRQoL: age > 75 or 75 and over, primary cancer, of the breast /prostate type and life expectancy > or < 6 months.

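### The primary QFS test and hazard ratio ignore the prognostic factors used in minimisation, and no adjusted treatment effect is pre-specified: valid, but it can cost power

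*Protocol article*

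**What the plan says.** In the protocol article, Randomisation: "Randomization is performed by minimization, with stratification according to the following criteria". Five factors follow, with different reasons:

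- Centre: "The cancer centre, as unknown heterogeneity in PC management could induce a bias".
- Designated relative: "The presence or absence of a designated person close, to obtain a well-balanced population in the two groups", for the sake of the caregiver outcomes.
- Age, primary cancer type and life expectancy, which alone are introduced as "The main indicators influencing prognosis and HRQoL".

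In Statistical analysis, the sample size is set "with a bilateral Type I error of 0.0166 and a statistical power of 80"%, for HR 0.5, from medians of 1 and 2 months, giving 88 events in 96 patients before attrition. For the primary endpoint: "The comparison between the two RCT groups will be performed using log-rank test". The HR comes from a univariate Cox model. Multivariate Cox models are added to explore what influences QFS. For these, "Variables with a *p*-value < 0.20 will be eligible for the multivariate model", the number of variables is limited to one per 10 events, and only the group term is forced in.

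**The concern.** Minimising on a prognostic factor makes the arms more alike on it than simple randomisation would. An analysis that leaves the factor out does not use that balance: its variance is too large for the design, so the test rejects too rarely under the null and loses power under the alternative. The Cox HR is also non-collapsible. When a prognostic factor is omitted, the estimated HR is a marginal one and lies nearer 1 than the HR within strata.

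The article itself names three minimisation factors as driving prognosis and HRQoL, then uses none of them in the primary comparison. It does not leave the choice open, since it names the test, the model, the screen and the forced term. The baseline score of the analysed dimension, from which the 10-point deterioration is measured, is not a planned covariate either. With 88 events planned for 80% power at 0.0166 there is little slack, and no adjusted treatment effect is fixed in advance to fall back on.

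**Working it through.** **1. The plan's own figure.** Inputs from Statistical analysis: HR 0.5, two-sided α 0.0166, power 80%, 1:1 allocation. Schoenfeld's formula:

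d = 4 (z₁₋α/₂ + z₁₋β)² / (ln HR)² = 4 (2.395 + 0.842)² / 0.6931² = 41.91 / 0.4805 = 87.2, rounded up to **88**.

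Power with 88 events: Φ(√88 / 2 × 0.6931 − 2.395) = Φ(0.856) = 80.4%. The stated figure is reproduced. It is a calculation for an unadjusted comparison.

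**2. Unadjusted against fully adjusted.** Simulation with 96 patients and 88 events, exponential times, minimisation with a biased coin of 0.8, and a true within-stratum HR of 0.5. Assumptions, because the article gives no factor effects: the same HR for each of age, cancer type and life expectancy; a modest centre effect; no effect of designated relative. The adjusted Cox model holds group and all five minimisation factors (eight parameters). There were 6,000 null and 4,000 alternative replicates. The Monte Carlo standard error is about √(0.75 × 0.25 / 4,000) = 0.7 points for power and √(0.0166 × 0.9834 / 6,000) = 0.17 points for type I error.

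| Assumed HR per factor | Type I error, log-rank | Type I error, adjusted | Mean unadjusted HR | Power, log-rank | Power, adjusted | Power, adjusted and size-corrected |
|---|---|---|---|---|---|---|
| 1.25 | 1.78% | 2.53% | 0.505 | 77.7% | 80.0% | 75.1% |
| 1.5 | 1.33% | 2.60% | 0.526 | 72.2% | 79.1% | 75.0% |
| 2.0 | 0.80% | 2.13% | 0.566 | 60.6% | 79.5% | 76.0% |

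The gain at the nominal level is 2.3, 6.9 and 18.9 points. After size correction it is −2.6, +2.8 and +15.4 points. With no prognostic effect at all (2,000 replicates) the mean unadjusted HR was 0.494, so the shift towards 1 comes from omitting the factors.

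**3. Unadjusted against a small model.** Cox model with group and the three named factors only; same design and within-stratum HR 0.5:

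| Assumed effects | Power, unadjusted | Power, three-factor Cox |
|---|---|---|
| Factor HR 1.25, baseline score HR 1.2 per SD (score not in model) | 74% | 76% |
| Factor HR 1.5 | 73% | 80% |
| Factor HR 2.0 | 60% | 80% |

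With factor HR 1.5 and baseline score HR 1.4 per SD, adding the score to the model gave 80%, against 67% unadjusted. Type I error was 0.6–1.7% unadjusted and 1.7–2.2% adjusted, against 1.66% nominal. A separate run at factor HR 1.5 (1,200 replicates) also gave 73% and 80%, with mean HRs of 0.526 and 0.489.

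**4. A larger model.** Age, cancer type, life expectancy, designated relative and baseline score, stratified by centre (five equal sites assumed): type I error 2.0–2.5%, mean HR 0.47–0.48 against a true 0.50, and power of 76% against 81% unadjusted when nothing is prognostic. This is too heavy for about 88 events.

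**5. Reading HR 0.5 as marginal.** In the simulation of step 2, the within-stratum HR was set to 0.49, 0.465 and 0.42 for the weak, moderate and strong cases, so that the mean unadjusted HR came out at 0.495, 0.491 and 0.490. Log-rank power was then 80.1%, 81.5% and 83.5%. Size-corrected adjusted power was 77.9%, 83.6% and 92.7%.

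**The case against.** The case for leaving the plan alone is substantial.

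- **The test is valid and matches the sample-size basis.** A reader might infer that the unadjusted analysis inflates type I error. It does not: the rates above are at or below nominal within simulation error. This stands.
- **HR 0.5 comes from group medians, so it is a marginal effect.** A reader might infer that the planned 80% power is lost or that the univariate HR is biased. Step 5 shows that the planned power holds on the marginal reading, and the univariate HR estimates the marginal effect on which the trial was sized. This stands. What remains is a loss relative to an adjusted analysis, which is present on either reading when the factors are moderate or strong.
- **Only three of the five factors are called prognostic.** Centre is included for possible heterogeneity and designated relative for the caregiver outcomes. Speaking of five prognostic factors would misread the Randomisation section. This stands.
- **The p < 0.20 screen belongs to an exploratory model.** It cannot affect the primary test or its HR. This stands. The gap is that no other adjusted estimate is planned.
- **The sizes are assumption-driven.** The article gives no factor effects, and the simulations use continuous event times although the QLQ-C30 is collected every 4 weeks ± 2. This stands as a limit on the figures, not on their direction when the factors are prognostic.
- **Adjustment is not free.** The larger models ran above nominal and gained nothing with weak factors. This argues for a small model.

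**Conclusion.** The point holds as one of efficiency and pre-specification, not of validity. The primary test and HR ignore three factors that the article itself names as prognostic and on which it minimises, and no adjusted treatment effect is fixed in advance.

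If the within-stratum HR is 0.5, the unadjusted test gives up about 2 points of power for weak factors (HR 1.25 each), 7 for moderate (1.5) and up to 20 for strong (2.0) at the nominal level. Size correction was computed only for the eight-parameter model. There it left no gain for weak factors, about 3 points for moderate and about 15 for strong. The unadjusted HR averages 0.505 to 0.566 where the within-stratum HR is 0.5; that is a different, marginal quantity rather than an error.

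These sizes rest on assumed factor effects, continuous event times and 88 events in 96 patients. The change should be made, because three of the four covariates are already recorded at allocation, the fourth is collected at baseline, and the possible gain is large compared with the cost.

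**What to change.** Before any outcome data by group are seen (the trial is open-label), pre-specify for each of the three dimensions a Cox model with group, age class, primary cancer type, life-expectancy class and the continuous baseline score of that dimension, with the group effect tested at 0.0166. If each factor has two classes, this is five parameters, or 88 / 5 = 17.6 events per parameter, well inside the article's limit of one variable per 10 events.

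- Keep the unadjusted log-rank test and univariate HR as sensitivity analyses. Examine centre and designated relative in sensitivity analyses only.
- Keep the p < 0.20 screened model for exploring factors, and say that it will not be used to estimate the treatment effect.
- Write out the classes as the randomisation system uses them, so that every patient has one level. The age classes as printed in Randomisation leave those under 75 without one.

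Cost: a paragraph in the statistical section and a few lines of code. The minimisation factors are known at randomisation, and Table 2 schedules the QLQ-C30 at the first visit. There are two downsides to state. The primary HR becomes conditional rather than marginal. With about 88 events the Wald test can also run slightly above nominal (about 1.7–2.2% against 1.66%), so keep the model small and consider a score or likelihood-ratio test.
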